#### Your tracking

Participants can opt to receive local air quality and step count information in real-time. The air quality feature displays location-specific air quality data sourced from www.airrater.org. This data includes PM_2.5_ (particulate matter with a diameter ≤ 2.5 micrometres) readings and health advice from the relevant state or territory health department, e.g., reduce outdoor physical activity if symptoms such as cough or shortness of breath arise when air quality is ‘fairly good’; and to stay inside with windows and doors closed if it is ‘poor.’ PM_2.5_ readings at the participant’s location are recorded throughout the trial. To track physical activity, the REBUILD app syncs with the Apple Health or Google Fit apps on the participants device, enabling step count and distance travelled to be displayed in-app for motivation.

#### Your diaries

Participants can record their medications, side effects, and supplemental oxygen use here and are encouraged to keep this information updated. The intervention group can also access the self-management content here.

#### Other information

Participants of both groups can record data such as ILD diagnosis, comorbidities and smoking history here. Phone and email technical support contact details are in this section and visible to all participants. In addition, the intervention group can access links to ILD-related educational resources, including videos, PDFs, and websites, as well as a one-way messaging inbox that can be used by the study team to alert participants to clinical trials of potential relevance to them. These components are not visible to the control group.

### Control group

The control group receive the same standard of clinical care as the intervention group, including regular ILD clinic reviews, meaning the medical management of both groups is the same. The control group also receive access to a reduced capability or ‘lite’ version of the REBUILD app for remote data collection and self-monitoring only. The lite version of the app does not include access to the educational materials or the self-management content but does include the physical activity and air quality features described above. To control for the effects of attention, participants in the control group will receive calls at the same frequency as the intervention group, however these calls will be general in nature with no health advice provided. Calls will be completed by site study coordinators, who will offer technical support only. Participants seeking health advice will be directed to their usual care providers.

At week 26, participants in the control group will receive access to the full version of the REBUILD app (Fig. 3) on ethical grounds, however this will not include access to the self-management package or the phone support provided in the intervention. This difference will be accounted for during the final data analysis.

**Fig. 3 Fig3:**
[figure not shown]
Study timeline

### Aims and outcomes

This study aims to compare the clinical efficacy and cost-effectiveness of the self-management package delivered through the REBUILD app to standard clinical care; and to understand the barriers and facilitators to adoption of the intervention. The study team hypothesise that REBUILD-SM will (1) improve HRQoL, symptoms, anxiety, self-efficacy, and physical activity in people with ILD; (2) be a cost-effective intervention compared to standard care; and (3) be implementable in clinical practice.

The primary outcome is change in HRQoL measured by change in King’s Brief Interstitial Lung Disease (K-BILD) questionnaire score at 12 weeks. The K-BILD has been chosen as a valid, ILD-specific measure of HRQoL with demonstrated responsiveness to interventions; [31] and this timepoint was selected based on evidence showing change in physiological variables at 12 weeks to be predictive of mortality and disease progression in IPF patients [32]. Pulmonary rehabilitation (commonly lasting between 8 and 12 weeks) has also demonstrated efficacy in improving short-term HRQoL in people with IPF, [33] suggesting that 12 weeks will be sufficient to observe a treatment effect.

The secondary outcomes are as follows (see also Table 1):

Change in K-BILD score from baseline at week 26 and 52; and change in EQ-5D-5L score from baseline at week 12, 26 and 52Change in General Self-Efficacy Scale (GSE) score from baseline at week 12, 26 and 52Change in Dyspnoea-12 score from baseline at week 12, 26 and 52Change in Hospital Anxiety and Depression Scale (HADS) score from baseline at week 12, 26 and 52Change in physical activity level from baseline at week 12 and 52Uptake or changes to ILD treatments, including clinical trial enrolment at week 12, 26 and 52Acceptability of the REBUILD app, evaluated utilising the mHealth App Usability Questionnaire (MAUQ) score at week 12, 26, and 52; and app analytics, including frequency the app and its individual features are accessed and used, total time of use and percentage of complete data enteredChange in eHealth and Literacy Scale (eHEALS) score from baseline at week 12 and 52Autonomy, which will be evaluated using the Healthcare Climate Questionnaire (HCCQ) at week 12

**Table 1 Tab1:** Study endpoints

**Data collection**	**Baseline**	**Week**			
		**12**	**26**	**38**	**52**
Demographic and clinical information	**X**		**X**		**X**
HRQoL (K-BILD & EQ-5D-5L questionnaire)	**X**	**X**	**X**		**X**
GSE	**X**	**X**	**X**		**X**
Dyspnoea-12	**X**	**X**	**X**		**X**
HADS	**X**	**X**	**X**		**X**
7 days physical activity monitoring (StepWatch)	**X**	**X**			**X**
Uptake or changes to treatments for ILD	**X**	**X**	**X**		**X**
All-cause hospitalisation / ED visits in last 12 months	**X**		**X**		**X**
Cost Diary	**X**	**X**	**X**	**X**	**X**
MAUQ		**X**	**X**		**X**
eHEALS	**X**	**X**			**X**
HCCQ		**X**			

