### Data collection

Study endpoints are completed using the REBUILD app, with push notifications informing participants when they have tasks to complete. Reminders will be sent at 24 and 48 h to encourage data completion, followed by a reminder phone call from sites if data is still pending at 72 h. An additional phone call will be completed if the endpoints remain outstanding after 5–7 days. Step count over a 7-day period will be measured at baseline, week 12 and 52 using the StepWatch activity monitor (Modus Health, Washington DC, USA), a reliable and validated tool used in patients with chronic lung disease [34]. Information on Emergency Department (ED) presentations and hospitalisations as well as uptake and changes to ILD treatment and clinical trial enrolment will be gathered from the participants’ electronic healthcare record.

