### Economic evaluation

Assessed using a cost diary administered via Research Electronic Data Capture (REDCap) link at baseline and week 12, 26, 38 and 52, as the complexity and length of the cost diary makes it unsuitable for in-app completion. Additional information will be drawn from state-base hospital records, Pharmaceutical Benefits Scheme (PBS) and Medicare Benefits Schedule (MBS) data, with existing approved linkage between these and the AILDR.

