#### Translational and behaviour change success

This will be assessed using the RE-AIM framework (Table 2) which aims to maximise implementation and integration of evidence-based health care interventions. This data will inform development of a Self-Management Toolkit, in partnership with key stakeholders, to accompany the digital package and facilitate adoption into local ILD services.

**Table 2 Tab2:** Implementation evaluation outcomes according to RE-AIM framework

RE-AIM element	Outcomes Assessed
Reach	Percent of eligible individuals who participate Characteristics of participants (age, sex, postcode, disease severity, HRQoL, eHEALS)
Effectiveness	Intervention completion (> 75% planned telephone sessions delivered) Number of self-management goals set (intervention group) Clinical outcomes, number of people who take up pulmonary rehabilitation, healthcare utilisation, adverse events Patient experience (semi-structured interviews)
Adoption	Intervention uptake (number who accessed the app on at least one occasion; number who attended start-up phone consultation and set a goal – intervention group) Frequency of app access (both groups) Characteristics of staff delivering intervention; staff time to get participants onto the app; number of occasions staff need to assist participant to get onto the app Health care professional experience (semi-structured interviews), clinical partner involvement
Implementation	Number of self-management modules accessed Modules delivered Adaptations made to intervention Staff time (from phone call record, both groups)
Maintenance	Individual: Use of REBUILD-SM, clinical outcomes at 6 months. Self-efficacy score as a marker for perceived self-management skills Organisation: Intent to continue using REBUILD-SM at 6 months post-trial completion, local funding models, modifications made

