#### Economic evaluation

Within trial cost effectiveness and cost-utility analyses will be conducted, and trial outcomes will be extrapolated to a 1, 2 and 5-year time horizons using a disease simulation model. Mean total costs (direct and indirect) will be assessed for both control and intervention groups. For modelling purposes beyond the trial period, mean total annual costs for ILD-related and all healthcare utilisations will be estimated, and appropriate discount rates applied. The mean effect between baseline and 52 weeks of both intervention and control groups will be assessed by measuring the change in primary outcome measure, the K-BILD (for cost-effectiveness analysis) and change in health state utility values and subsequently quality-adjusted life-years (QALYs) derived from the EQ-5D-5L questionnaire (for the cost utility analysis). Appropriate discount rates will be applied for modelling purposes beyond the trial period. The incremental cost effectiveness (ICER)/incremental cost utility (ICUR) ratio will be assessed and compared between each group. To address any uncertainty around estimates, uncertainty, sensitivity, and subgroup analyses will be conducted. Disease simulation modelling will then be conducted to project within-trial outcomes beyond the trial period at 1, 2 and 5-year time horizons. Using Markov simulation modelling, we will determine and compare total time horizon costs, QALYs, and future ICER/ICUR between intervention and control groups.

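### The 12-month look-back for hospitalisations and ED visits does not fit the week-26 visit: about half of that window precedes randomisation

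*Protocol article*

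**What the plan says.** Table 1 of the protocol article, titled "Study endpoints", has a single row for this item, "All-cause hospitalisation / ED visits in last 12 months", marked at baseline, week 26 and week 52. The Data collection section names the source: "Information on Emergency Department (ED) presentations and hospitalisations" are taken from the electronic healthcare record. It gives no time window and does not say whether event dates are stored.

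The written list of secondary outcomes (Aims and outcomes) does not name hospitalisation or ED visits, though it points the reader to Table 1. Table 2 puts healthcare use under the RE-AIM element Effectiveness: "Clinical outcomes, number of people who take up pulmonary rehabilitation, healthcare utilisation, adverse events". The Control group section says that control participants receive the full app at week 26, without the self-management package or phone support, and that the final analysis will take account of this.

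**The concern.** A follow-up count is meant to show what happened after randomisation. Events before randomisation cannot be affected by the allocated arm, so including them pulls a between-arm comparison towards no difference. A 12-month look-back at a visit only 26 weeks after randomisation necessarily includes such events.

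Week 26 also divides the follow-up. Before it, control participants have only the reduced app; after it, they have the full one. To allow for that change in healthcare use, the analyst needs events in weeks 0–26 and weeks 26–52 as separate quantities. The windows as labelled supply neither.

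**Working it through.** The article states no figure for this item, so there is none to reproduce. The check is interval arithmetic on the windows.

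**Inputs.** Look-back of 12 months and visits at baseline, week 26 and week 52 (Table 1). Week 26 is day 26 × 7 = 182; week 52 is day 52 × 7 = 364. Assumptions: baseline and randomisation are both day 0, and 12 months is 365 days.

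**Windows.** Each runs from (visit day − 365) to the visit day.

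| Visit | Window (days) | Days before randomisation |
|---|---|---|
| Baseline | −365 to 0 | 365 (as intended) |
| Week 26 | −183 to 182 | 183 of 365 = 50.1% |
| Week 52 | −1 to 364 | 1 of 365 = 0.3% |

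With a year of 364 or 365.25 days, the pre-randomisation part is 182 or 183.25 days at week 26, and 0 or 1.25 days at week 52.

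**Overlap.** Baseline and week 26 share days −183 to 0, which is 183 days. Week 26 and week 52 share days −1 to 182, which is 183 days and essentially all of weeks 0–26.

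**Dilution at week 26.** Assume a constant event rate that is the same before randomisation in both arms and after randomisation in the control arm. With true post-randomisation rate ratio R:

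apparent ratio = (183 + 182 × R) / 365

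- R = 0.80: (183 + 145.6) / 365 = 0.90
- R = 0.70: (183 + 127.4) / 365 = 0.85
- R = 0.50: (183 + 91) / 365 = 0.75

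The article gives no event rate or expected effect for this item, so these values of R are illustrations. The equal-rate assumption can be varied. If the pre-randomisation rate is k times the later control rate, the apparent ratio is (183k + 182R) / (183k + 182). For R = 0.80:

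- k = 0.5: (91.5 + 145.6) / (91.5 + 182) = 237.1 / 273.5 = 0.87
- k = 2: (366 + 145.6) / (366 + 182) = 511.6 / 548 = 0.93

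**Same check at week 52.** (1 + 364 × R) / 365 gives 0.80 for R = 0.80 and 0.70 for R = 0.70. There is no material dilution.

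**Can the periods be recovered from counts?** Call the half-years A (weeks −52 to −26), B (−26 to 0), C (0 to 26) and D (26 to 52). The three records give A + B, B + C and C + D: three totals for four unknowns. Subtracting the second from the third gives D − B, not D. No combination of the three totals isolates C or D.

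**The case against.** The strongest reply is that little is lost. The data come from a healthcare record rather than from recall, so if events carry dates they can be assigned to the right period at analysis. The row label may be shorthand in a condensed article for a form that gives the window visit by visit. The item is not among the listed secondary outcomes or the key secondary analyses, and no test at week 26 is described for it.

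Much of this stands, and it limits the severity. It does not remove the point. The article does not say that dates are captured, and the only look-back it states is wrong for one of the two follow-up visits.

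A reader might infer four stronger things that the document does not support:

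- **That week 52 also counts pre-randomisation events.** Its window is the post-randomisation year to within about a day, and it compares directly with the baseline year.
- **That events are in fact counted twice.** Events in weeks 0–26 fall in both follow-up windows, but they are double counted only if the two records are added or treated as separate periods. Nothing in the article says so.
- **That the cost analysis is corrupted.** The economic evaluation plans that "mean total annual costs for ILD-related and all healthcare utilisations will be estimated", but it has its own sources: a cost diary at five time points and, beyond that, "Additional information will be drawn from state-base hospital records" and linked pharmaceutical and medical benefits data. No section says that costs are built from this Table 1 row.
- **That a planned test loses a known amount of power.** No such test is stated, so a loss of power cannot be tied to the plan.

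**Conclusion.** The point holds for week 26. Followed as written, about half of that window (183 of 365 days) precedes randomisation and repeats baseline data. A true rate ratio of 0.80 would then appear as about 0.90 if event rates are equal before and after, or between 0.87 and 0.93 if the earlier rate is half or twice the later control rate. Recorded as undated counts, the three totals also cannot separate weeks 0–26 from weeks 26–52, the point at which control access to the app changes. Double counting is a risk only if the two follow-up records are added.

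Severity is minor to moderate. It touches healthcare use as a Table 1 endpoint and as a RE-AIM effectiveness outcome. The primary outcome, the listed secondary outcomes and the week-52 12-month count are not affected.

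**What to change.** State the look-back for each visit in Table 1 and on the data form:

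- baseline: the 12 months before baseline;
- week 26: randomisation to week 26;
- week 52: week 26 to week 52.

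Record the date of each event from the electronic healthcare record. The two follow-up records then have no overlap and no pre-randomisation time, and together they cover the full post-randomisation year (182 + 182 = 364 days), which can still be compared with the baseline year.

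The cost is an edit to one table row and one form, plus re-extraction of event dates for participants already enrolled. That should be possible provided the record holds dates, which the article does not state. Enrolment began in June 2024 and was expected to finish by December 2026, so an early change leaves less to re-extract.

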### Data collection

Study endpoints are completed using the REBUILD app, with push notifications informing participants when they have tasks to complete. Reminders will be sent at 24 and 48 h to encourage data completion, followed by a reminder phone call from sites if data is still pending at 72 h. An additional phone call will be completed if the endpoints remain outstanding after 5–7 days. Step count over a 7-day period will be measured at baseline, week 12 and 52 using the StepWatch activity monitor (Modus Health, Washington DC, USA), a reliable and validated tool used in patients with chronic lung disease [34]. Information on Emergency Department (ED) presentations and hospitalisations as well as uptake and changes to ILD treatment and clinical trial enrolment will be gathered from the participants’ electronic healthcare record.

### Economic evaluation

Assessed using a cost diary administered via Research Electronic Data Capture (REDCap) link at baseline and week 12, 26, 38 and 52, as the complexity and length of the cost diary makes it unsuitable for in-app completion. Additional information will be drawn from state-base hospital records, Pharmaceutical Benefits Scheme (PBS) and Medicare Benefits Schedule (MBS) data, with existing approved linkage between these and the AILDR.

### Implementation evaluation

To underpin any future implementation, we aim to understand the barriers and facilitators to adoption of REBUILD-SM by people with ILD as well as healthcare professionals using the following methods.

#### Participant experience

Following completion of the 12-week intervention, semi-structured telephone interviews will be undertaken with a purposive sample of intervention group participants. These interviews aim to facilitate understanding of the patient experience and will be conducted by a researcher not involved in delivering the intervention. A sampling framework will be used to select participants and interviews will be recorded and transcribed verbatim. An interview guide will be used, and qualitative data obtained from these interviews will be analysed using the principles of grounded theory [35]. Recruitment will continue until data saturation is achieved.

#### Healthcare professional experience

Qualitative interviews will be undertaken with healthcare professionals involved in the trial during the last 26 weeks of recruitment at their site. An interview guide will be used, and interviews will be completed via phone, recorded and transcribed verbatim. The aim of these interviews is to understand the healthcare professionals’ experience of REBUILD-SM and the use of a technology-based intervention to deliver the intervention. The Theoretical Domains Framework [36] will be used to understand behaviours that function as barriers or facilitators to the implementation of the intervention into clinical practice.

#### Translational and behaviour change success

This will be assessed using the RE-AIM framework (Table 2) which aims to maximise implementation and integration of evidence-based health care interventions. This data will inform development of a Self-Management Toolkit, in partnership with key stakeholders, to accompany the digital package and facilitate adoption into local ILD services.

**Table 2 Tab2:** Implementation evaluation outcomes according to RE-AIM framework

RE-AIM element	Outcomes Assessed
Reach	Percent of eligible individuals who participate Characteristics of participants (age, sex, postcode, disease severity, HRQoL, eHEALS)
Effectiveness	Intervention completion (> 75% planned telephone sessions delivered) Number of self-management goals set (intervention group) Clinical outcomes, number of people who take up pulmonary rehabilitation, healthcare utilisation, adverse events Patient experience (semi-structured interviews)
Adoption	Intervention uptake (number who accessed the app on at least one occasion; number who attended start-up phone consultation and set a goal – intervention group) Frequency of app access (both groups) Characteristics of staff delivering intervention; staff time to get participants onto the app; number of occasions staff need to assist participant to get onto the app Health care professional experience (semi-structured interviews), clinical partner involvement
Implementation	Number of self-management modules accessed Modules delivered Adaptations made to intervention Staff time (from phone call record, both groups)
Maintenance	Individual: Use of REBUILD-SM, clinical outcomes at 6 months. Self-efficacy score as a marker for perceived self-management skills Organisation: Intent to continue using REBUILD-SM at 6 months post-trial completion, local funding models, modifications made

## Statistical considerations

### Sample size justification

A sample size of 400 subjects randomised equally between groups will provide at least 82% power with 95% two-sided confidence to identify a five K-BILD unit improvement from the usual care mean of 55.3 (SD 15.6), with a 5-unit increase considered the minimum clinically important difference [31]. Assuming a pooled SD of 6.5% this offers >95% power to identify a statistically significant difference between groups of 5 points in K-BILD score (change of + 2 in control and + 7 in active arm), allowing for up to 15% of randomly missing endpoint data. Even for a difference of 3 points in Z-score, the study will similarly offer 95% power. This sample size allows for a modest dropout rate of 10%.

Participant mortality should not negatively impact the primary endpoint data as participants expected to die during the 12 week trial period are excluded. Randomisation will be performed using the method of minimisation stratified by (i) FVC: ≤50% or ≥ 51%; (ii) IPF: yes/no; and (iii) treating site.

### Data analysis

#### Quantitative analysis

The primary endpoint is the difference from baseline in K-BILD scores at 12 weeks according to the intention-to-treat principle. Primary analysis will evaluate whether these differences are larger in the intervention group compared to the control group using 2-sided tests at a 5% level of significance. Key secondary analyses will evaluate the proportion of those with 12-week K-BILD scores above and below 50 and whose K-BILD has increased from baseline by at least 5 units. Additional analyses of secondary endpoints will be performed using standard statistical tests as appropriate.

Associations between 12-week K-BILD score and key baseline variables will be evaluated. Acceptability outcome measures will be reported using the MAUQ. Feasibility will be measured as adherence to the clinical trial (defined as at least 80% completion of data questionnaires). Participants will be considered adherent to the intervention if they receive at least 75% of planned self-management phone calls and access the self-management website on at least one occasion. Percentage of completed modules will also be reviewed, as well as weekly time spent using the app during the study period. The primary and key secondary outcomes will be evaluated in subjects who remain adherent to the intervention in a per protocol analysis.

Analysis of the effect of the REBUILD-SM intervention in key subgroups will also be performed. These subgroups include FVC ≤ 50% or FVC ≥ 51%; IPF yes/no; time since ILD diagnosis < 12 months or ≥ 12 months; and age < 65 or ≥ 65 years.

Modus Research software will be used to retrieve StepWatch data. Participants will be asked to record their activity for 7 consecutive days, and up to 5 complete days of data will be used, with the first and last days of the activity period discarded due to incompleteness. Days with less than 200 steps or less than 24 h of recording time will also be discarded. Average steps per day over all included days will be calculated and difference in measures of physical activity between baseline and week 12 will be compared between groups.

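### The primary comparison of 12-week K-BILD change states no adjustment for baseline K-BILD or the randomisation factors; adding it is a free gain in precision of uncertain, possibly small, size

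*Protocol article*

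**What the plan says.** In the protocol article, the Quantitative analysis section defines the outcome: "The primary endpoint is the difference from baseline in K-BILD scores at 12 weeks according to the intention-to-treat principle". The comparison between arms follows: "Primary analysis will evaluate whether these differences are larger in the intervention group compared to the control group using 2-sided tests", at the 5% level. No model and no covariates are named. The relation of week-12 scores to baseline characteristics is listed as a separate evaluation, not as part of the primary comparison.

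Two binary K-BILD endpoints are key secondary analyses: "the proportion of those with 12-week K-BILD scores above and below 50", and a gain of at least 5 units. No covariates are stated for these either.

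The Sample size justification is a plain comparison of two means: "A sample size of 400 subjects randomised equally between groups will provide at least 82% power with 95% two-sided confidence" for a 5-point difference with SD 15.6. A second scenario takes a pooled SD of 6.5 beside a "change of + 2 in control and + 7 in active arm". The same section says "Randomisation will be performed using the method of minimisation stratified by" FVC, IPF status and site. The section on randomisation and blinding names the same three factors but describes permuted blocks.

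**The concern.** The endpoint wording, the unspecified two-sided test, the two-means sample size and the separate line on baseline associations together read most naturally as an unadjusted two-group test of change scores.

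Subtracting baseline fixes its coefficient at 1. A model that includes baseline estimates that coefficient and, in large samples, is never less precise. Regression to the mean also makes the change score over-correct: an arm that happens to start higher will look slightly worse. Finally, if allocation is balanced on prognostic factors that the analysis then ignores, the standard error tends to be too large and the test conservative.

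What is at stake is precision and sensitivity to chance imbalance, not validity. Baseline K-BILD is measured in every participant and the three factors must be entered before randomisation, so the information is already in hand.

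**Working it through.** **Inputs from the protocol article (Sample size justification).** 400 participants, 1:1, so 200 per arm; 15% missing endpoint data leaves 200 × 0.85 = 170 per arm; difference 5 points, and 3 points as a smaller effect; SD 15.6 and pooled SD 6.5; two-sided 5%.

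**Assumptions.** The correlation r is not given. I take the same SD at both visits and in both arms, so the slope on baseline equals r. Power uses the normal approximation: Φ(δ / (SD√(2/n)) − 1.96).

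**The plan's own figures.** With SD 15.6 and δ = 5, power is 89.4% at 200 per arm, 86.0% at 180 (10% dropout) and 84.0% at 170 (83.8% by t-test). The claim of at least 82% is met in each case; it falls to about 80% only if both losses are compounded (200 × 0.85 × 0.90 = 153 per arm). With SD 6.5 at 170 per arm, power is above 99.9% for 5 points and 98.9% for 3 points, so both 95% claims are met.

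**Formulas.**
- SD of change = 15.6 √(2(1 − r))
- Residual SD adjusted for baseline = 15.6 √(1 − r²)
- Variance ratio, adjusted to change = (1 − r²) / (2(1 − r)) = (1 + r)/2
- Share of a baseline difference left in the change-score estimate = 1 − r, with opposite sign
- SE of the baseline difference at 170 per arm = 15.6 √(2/170) = 1.69 points

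**What r do the document's SDs imply?** If 15.6 is the score SD and 6.5 the SD of change, r = 1 − 6.5² / (2 × 15.6²) = 1 − 42.25/486.72 = 0.913. If instead 15.6 were both the score SD and the SD of change, 2(1 − r) = 1 and r = 0.5.

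**Results at 170 per arm (change score → baseline-adjusted).**

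| r | SD | Variance gain | Power, 5 points | Power, 3 points | Shift from a 1-SE baseline imbalance |
|---|---|---|---|---|---|
| 0.5 (assumed) | 15.60 → 13.51 | 25% | 84.0% → 92.7% | 42.6% → 53.5% | 0.85 points |
| 0.7 (assumed) | 12.08 → 11.14 | 15% | 96.8% → 98.5% | 62.9% → 69.9% | 0.51 points |
| 0.8 (assumed) | 9.87 → 9.36 | 10% | 99.7% → 99.8% | 80.0% → 84.0% | 0.34 points |
| 0.913 (from 15.6 and 6.5) | 6.50 → 6.36 | 4.3% | above 99.9% for both | 98.9% → 99.2% | 0.15 points |

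**Randomisation factors.** The documents do not say how much of the variance FVC stratum, IPF and site explain, so their contribution cannot be computed. The cost of carrying them is small: arm, baseline, FVC, IPF and four sites use 1 + 1 + 1 + 1 + 3 = 7 degrees of freedom plus the intercept, leaving 332 of 340.

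**The case against.** The strongest reply is that the absence of adjustment is inferred from silence. The article fixes the endpoint, the sidedness and the significance level; it names no t-test and excludes no covariate. A change endpoint is compatible with covariance analysis, since modelling change or the week-12 score with baseline as a covariate gives the same treatment effect. Covariate lists commonly sit in a statistical analysis plan, and none is shown here. This stands in part: one cannot say that the trial will ignore baseline, only that the stated analysis does not mention it. It does not remove the point, because the analysis that is described has a better alternative that costs nothing.

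The second reply is that the gain may be trivial. The pooled SD of 6.5 stands next to the two changes from baseline and most naturally reads as an SD of change; on that reading the gain is about 4%, and power is ample either way. This also stands, with the caveat that the figure carries a percent sign and is followed by a mention of Z-scores, so the reading is not certain.

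A reader might infer more than the documents support:
- That the primary result would be biased or its test invalid. It would not: the change-score comparison is unbiased under randomisation, and ignoring balanced factors tends to be conservative.
- That the trial forgoes a large, known amount of power. The larger gains in the table rest on an assumed r.
- That a specific loss from ignoring FVC, IPF and site can be stated. Any such figure needs a share of variance explained, for which there is no source.
- That the proportions above and below 50 are a separate flaw. No power is claimed for that endpoint; it simply benefits from the same covariates.

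**Conclusion.** The point holds as a free improvement. As written, the primary analysis is a between-arm comparison of 12-week K-BILD change with no adjustment stated; it is valid, but in large samples never more precise than a model adjusted for baseline. The variance gain is about 4% if 15.6 and 6.5 are the score SD and the SD of change, and 10% to 25% for an assumed r of 0.8 to 0.5. Only towards the lower end of that range does it change power for the 5-point difference materially. These figures rest on equal SDs at both visits and on 15% missing data. The contribution of the three randomisation factors remains unquantified. Stating the model in advance also closes a later choice between adjusted and unadjusted results.

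**What to change.** State the primary analysis as a linear model of week-12 K-BILD, or equivalently of change, on arm, baseline K-BILD, FVC stratum, IPF status and site, with the arm coefficient, its 95% confidence interval and the two-sided 5% test as the primary result. Analyse the two binary K-BILD endpoints by logistic regression with the same covariates. If an analysis plan already specifies this, it is enough to bring the protocol wording into line with it.

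The protocol's two descriptions of the allocation method, permuted blocks and minimisation, should be reconciled at the same time. The covariate list does not depend on the outcome, because both descriptions name the same three factors.

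The cost is one or two sentences before database lock. No new data, visits or participants are needed; enrolment is planned to run to December 2026.
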